### Data Analysis

Data will be analyzed using SAS version 9.4 (SAS Institute). The recruitment rate will be calculated as the number of registered participants divided by the total number of Macquarie University graduates in 2018. The denominator data will be supplied by the Macquarie University Graduation Office. The opt-in rates for data linkage of health records and survey responses will be calculated as the number of registered participants opting in divided by the number of registered participants. The representativeness of the sample will be evaluated by comparing its demographic profile with that of the full graduating cohort. Survey drop-out rates will be calculated separately for the baseline and follow-up surveys as the number of participants completing the survey divided by the number of participants starting the survey. Descriptive statistics will be used to evaluate the completeness of the baseline and follow-up surveys. The retention rate of the sample will be calculated as the number of participants completing the follow-up survey divided by the number of participants completing the baseline survey.

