## Results

Participant recruitment was completed in October 2018, and data collection for the baseline and follow-up surveys was completed in November 2019. As of April 2020, the process of acquiring health records from administrative data collections has commenced. The findings of this pilot cohort study will be prepared for publication in mid-2020. These findings will include the opt-in and opt-out rates for data linkage of health records and survey responses; a description of the representativeness of recruited participants; a description of the completeness of baseline and follow-up online survey items; and attrition rates for the 12-month follow-up survey.

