## Discussion

Emerging adulthood is a unique segment of an individual’s life course. The defining features of this transitional period include identity exploration, instability, possibilities, self-focus, and feeling in-between adolescence and adulthood, all of which are thought to impact quality of life, health, and well-being. A longitudinal cohort study with a comprehensive set of measures would facilitate greater understanding of the multi-faceted elements and unique challenges that contribute to the health and well-being of emerging adults. Before expending significant resources on a large, longitudinal cohort study, it is advisable to first test the feasibility and inform the development of the larger study.

This pilot cohort study aims to evaluate the feasibility of recruiting Australian university graduates to establish a longitudinal cohort study to inform our understanding of emerging adulthood. It will evaluate the ability to recruit university graduates and obtain good quality survey data on a wide range of relevant measures. It is vital to obtain estimates of recruitment, response, and retention (or attrition) rates because these will inform the sample size and statistical power calculations that are necessary for planning and designing a future longitudinal cohort study. An evaluation of the measures in the pilot study is also necessary for the development and selection of the measures to be included in the main study.

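### The survey drop-out rate is defined as completers over starters, which is the completion rate, so the reported figure would be the complement of drop-out.

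*Protocol article*

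**What the plan says.** In the protocol article, Methods, Data Analysis, the name and the formula stand in one sentence: "Survey drop-out rates will be calculated separately for the baseline and follow-up surveys as the number of participants completing the survey divided by" the number who start it. The ratio in full is "the number of participants completing the survey divided by the number of participants starting the survey".

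The same paragraph defines three other rates: recruitment, opt-in to data linkage, and retention. Retention reads: "The retention rate of the sample will be calculated as the number of participants completing the follow-up survey divided by" the number who completed the baseline survey. Completeness is covered separately: "Descriptive statistics will be used to evaluate the completeness of the baseline and follow-up surveys".

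The Discussion says what the pilot's rates are for: "It is vital to obtain estimates of recruitment, response, and retention (or attrition) rates", because "these will inform the sample size and statistical power calculations" for the later cohort.

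**The concern.** A drop-out rate counts people who begin and do not finish. The stated formula counts those who do finish. If the analysis follows the sentence literally, a survey that nearly everyone completes is reported as one that nearly everyone abandons.

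This is a feasibility pilot, so its rates are its results. The third and fourth aims in the Introduction concern whether survey data can be obtained at baseline and again at 12 months. Among the rates the article defines, this one shows most directly whether people who open a survey of about 25 minutes reach the end. A wrong label on it would mislead a reader on that question for both surveys. The sentence alone also does not show whether the name or the formula was intended.

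**Working it through.** The article states no rate, count or sample size that could be reproduced here, so this is a check of a definition.

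**Inputs.** Let S be the number starting a survey and C the number completing it. Both terms come from the Data Analysis sentence. Their values are not given, so every number below is an assumption for illustration.

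**Formula as written:** C / S.

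**Drop-out rate:** (S − C) / S = 1 − C / S.

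**Relation:** C / S + (S − C) / S = 1. The two are exact complements and are equal only when C / S = 0.5.

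**Example.** S = 560, C = 490:
- as written: 490 / 560 = 0.875, or 87.5%
- drop-out: (560 − 490) / 560 = 70 / 560 = 0.125, or 12.5%

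**Range of assumed completion:**

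| C / S (reported as drop-out) | True drop-out |
|---|---|
| 50% | 50% |
| 60% | 40% |
| 70% | 30% |
| 80% | 20% |
| 90% | 10% |
| 95% | 5% |

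The better the survey performs, the larger the discrepancy. A value near 50% is the hardest to recognise as inverted, though the discrepancy there is also smallest.

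**Comparison with the neighbouring definitions:**
- Recruitment is registered participants over all 2018 graduates. Name and formula agree.
- Opt-in is those opting in over those registered. Name and formula agree.
- Retention is follow-up completers over baseline completers. Name and formula agree.
- Survey drop-out is completers over starters. Name and formula disagree.

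No other section redefines drop-out or supplies the complement. The mismatch is therefore an isolated slip and not a convention used throughout the article.

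**The case against.** The strongest reply is that little depends on this rate. Numerator and denominator are written out beside the label, so a reader who has the definition can subtract the result from one and nothing is lost. No threshold, progression criterion or decision rule is attached to it. Neither the Abstract, nor the aims, nor the list of planned findings in Results mentions drop-out within a survey by name. Completeness is to be described separately. Data collection had ended by November 2019, so no data are affected. All of this stands, and it limits the consequences. It does not make the sentence correct: a later report that prints a drop-out percentage without repeating the formula would be wrong.

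Two stronger readings are tempting, and the article does not support them.

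- *A reader might infer that the main study will be mis-sized.* Using an inverted rate d in n / (1 − d) would do real damage. With an assumed n of 300 and 80% completion, 300 / (1 − 0.80) = 1500 against 300 / (1 − 0.20) = 375. But the Discussion names recruitment, response and retention or attrition as the sizing inputs, not drop-out within a survey. Retention is correctly defined. The calculation needs an assumed n and a misuse that the article does not plan.
- *A reader might infer that the error recurs elsewhere.* Results promises "attrition rates for the 12-month follow-up survey", and the Discussion pairs retention with attrition. Both most naturally refer to loss between baseline and 12 months, the counterpart of the retention rate. Neither uses the ratio of completers to starters, and neither is wrong.

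**Conclusion.** The point holds as an error of definition in one sentence of Data Analysis. As written, the survey drop-out rate is the completion rate, and for both surveys the reported figure would be one minus the true drop-out. That conclusion is algebraic and needs no assumption. Only its numerical size does: 87.5% against 12.5% in the example, and from no discrepancy at 50% completion to 95% against 5% at 95% completion.

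It is a small correction and does not threaten the study. It would misstate one prespecified feasibility rate relevant to the third and fourth aims. It leaves recruitment, opt-in, retention and the collected data untouched, and its effect on later sample size planning is potential only.

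**What to change.** Change the sentence in Data Analysis in one of two ways:

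- keep the name and define the rate, for each survey, as (number starting − number completing) / number starting; or
- keep the ratio and call it the survey completion rate.

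Either is sufficient. The second needs no change to any program that already computes the stated ratio. In both cases, report the numbers of starters and completers beside the percentage, so that its direction is clear.

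The cost is one sentence, with no new data. It should be settled before the rate is reported. No change is needed in Results or the Discussion.

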## Results

Participant recruitment was completed in October 2018, and data collection for the baseline and follow-up surveys was completed in November 2019. As of April 2020, the process of acquiring health records from administrative data collections has commenced. The findings of this pilot cohort study will be prepared for publication in mid-2020. These findings will include the opt-in and opt-out rates for data linkage of health records and survey responses; a description of the representativeness of recruited participants; a description of the completeness of baseline and follow-up online survey items; and attrition rates for the 12-month follow-up survey.

## Discussion

Emerging adulthood is a unique segment of an individual’s life course. The defining features of this transitional period include identity exploration, instability, possibilities, self-focus, and feeling in-between adolescence and adulthood, all of which are thought to impact quality of life, health, and well-being. A longitudinal cohort study with a comprehensive set of measures would facilitate greater understanding of the multi-faceted elements and unique challenges that contribute to the health and well-being of emerging adults. Before expending significant resources on a large, longitudinal cohort study, it is advisable to first test the feasibility and inform the development of the larger study.

This pilot cohort study aims to evaluate the feasibility of recruiting Australian university graduates to establish a longitudinal cohort study to inform our understanding of emerging adulthood. It will evaluate the ability to recruit university graduates and obtain good quality survey data on a wide range of relevant measures. It is vital to obtain estimates of recruitment, response, and retention (or attrition) rates because these will inform the sample size and statistical power calculations that are necessary for planning and designing a future longitudinal cohort study. An evaluation of the measures in the pilot study is also necessary for the development and selection of the measures to be included in the main study.

There are challenges with recruiting university graduates into cohort studies using web-based surveys. Selection bias is an important consideration as many studies conducted among students report response rates below 20% [29-31]. University students and graduates frequently receive requests to participate in surveys, and this over-surveying can potentially lead to survey fatigue and poor response rates [32]. Compounding the issue is that the average response rate of web surveys is approximately 10% lower than that of mail or telephone surveys [33]. Student engagement, lottery incentives, and extra reminders can be effective for increasing the overall response rate [32,34-36]. However, merely increasing response rate does not necessarily entail diversifying or improving the representativeness of the sample [32]. Although self-selection can lead to unreliable survey outcomes [37], there are potential methods for correcting for selection biases (eg, poststratification or weighting class adjustments, propensity score adjustments, and generalized regression modelling [38]). It has been suggested that student surveys with a 10% or lower response rate can eventually be considered trustworthy if the response quality is good [34].

Response bias is another pervasive problem in the design of surveys. The many types of bias are question design (eg, problems with wording, leading questions, faulty scales, intrusiveness), questionnaire structure (eg, formatting, priming, length, response fatigue), administration of questionnaire (eg, respondent’s learning, recall, primacy or recency depending on mode) [39,40]. Some of these biases can be minimized by adopting previously validated instruments and scales. In the present study, the baseline and follow-up surveys are comprised almost entirely of commonly used and previously validated instruments and scales.

As to limitations, the study is modest in scale, and will be conducted at a single Australian university. This may not be representative of the broader population of university graduates in Australia.

In conclusion, this pilot study comes at a crucial time for research of this kind. It is expected that the findings from the pilot will identify areas for improvement and inform the development of a future longitudinal cohort study.

## Abbreviations

ACTRN: Australian New Zealand Clinical Trials Registry
BRS: Brief Resilience Scale
CHeReL: Centre for Health Record Linkage
EQ-5D: EuroQoL 5-dimension
GAD-7: General Anxiety Disorder scale
HRQOL: health-related quality of life
K10: Kessler Psychological Distress Scale
MQ-MINDS: Macquarie University – Monitoring of Injury and Psychosocial Health Outcomes, Career Trajectories and Continuing Education, Lived Experiences, and Social Connectedness
MSPSS: Multidimensional Scale of Perceived Social Support
RBS: Role Balance Scale
SF-12: Short Form Health Survey
SIAS-6: Social Interaction Anxiety Scale
SRRS: Social Readjustment Rating Scale
